**TITLE:** Controlled, double-blind, randomized trial to assess the efficacy and safety of hydroxychloroquine chemoprophylaxis in SARS CoV2 infection in healthcare personnel in the hospital setting (SANsinCOVID).

**Promoter:** Instituto de Investigación Valdecilla (IDIVAL)

**Code:** SANsinCOVID

**EudraCT:** 2020-001704-42

**Main investigators:** [name]. Jefe Servicio Digestivo

[name]. Jefe Servicio Infecciosas

**Collaborating investigators:** [name]. Jefe Servicio Medicina Interna

[name]. Jefe Servicio Neumología

[name]. Jefe Servicio Preventiva.

[name]. Jefe S. Riesgo Laborales

[name]. Jefe Servicio Inmunología

[name]. Reumatología

[name]. Servicio Farmacia Hospitalaria

**Funding:** This study has no source of funding.

**Contact:** - Clinical Research and Clinical Trials Unit Marqués de Valdecilla University Hospital

- [name].

- Santander Tel .: [name] [contact]

- Email: [[contact]](mailto:[contact])

1. **Summary**

Health professionals have a high risk of SARS CoV2 infection as evidenced by the data observed in China, Italy and Spain (about 10,000 at the moment, 12-15% of all registered cases, data from the Ministry of Health). This risk is higher in professionals who work in high risk areas where aerosols can be produced. Hydroxychloroquine (HDQ) has been shown to inhibit coronavirus in vitro, although very little clinical results are available. HDQ is a widely used, low-cost, limited-toxicity drug. Currently, there is no type of exposure prophylaxis that has proven to be useful against SARS CoV2. For this reason, we intend to develop a randomized, double-blind, controlled clinical trial with two parallel groups (200 mg of HCQ per day versus placebo) with a prophylaxis duration of 60 days.

**2. Hypothesis**

Our hypothesis is that HDQ chemoprophylaxis is capable of preventing SARS CoV-2 infection in a group at high risk of infection due to their occupational exposure and, alternatively, if it does not decrease the incidence of infection, it could be able to reduce severity. of the disease by said virus. In addition, it could potentially avoid the loss of working hours of highly qualified professionals essential in times of saturation of our health system.

1. **Objectives**

**Main objective**:

1. To evaluate the efficacy of HCQ prophylaxis for 2 months versus placebo in the prevention and reduction of symptomatic and asymptomatic SARS CoV-2 infection in healthcare personnel.

**Secondary objectives**.

1) Evaluate the safety of HDQ for 2 months in healthcare personnel.

2) Evaluate the number of working days lost as a consequence of symptomatic or asymptomatic infection by COVID19.

3) Analyze the percentage of severe respiratory disease by COVID-19 in healthcare personnel.

4) Define the incidence, prevalence and severity of SARS CoV-2 infection in healthcare personnel in the hospital setting.

**3. Study design.** Prospective, randomized and controlled. The medication will be manufactured in the Pharmacy of the Marqués de Valdecilla University Hospital. Two groups will be analyzed with a 1: 1 randomization.

**1) Chemoprophylaxis group (n = 225):** One 200 mg HDQ tablet once daily for two months.

**2) Control group (n = 225):** One placebo tablet (identical to that of the drug) once a day for two months.

1. **Study population.** It will include 450 health professionals who are working in areas of high exposure and high risk of transmission of SARS CoV2 (professionals from the Hospital in COVID areas, Intensive Care Unit, Emergencies, Anesthesia and all those who carry out procedures that generate aerosols).

**4. Duration of the study:**

25 weeks, distributed as follows:

- Recruitment period: Eight weeks from the inclusion of the first subject to the inclusion of the last study individual.

- Screening period: After signing the informed consent, an IgG serology and PCR of coronavirus will be carried out, the result of which will be obtained in a maximum period of 7 days. After obtaining a negative result, the study subject will begin taking the corresponding medication.

- Eight weeks of chemoprophylaxis vs placebo.

- Eight weeks for database debugging and analysis of results. Preliminary publication of the first results.

**4. Case definition:**

- **Symptomatic case:** Symptomatic COVID-19 infection defined as cough, dyspnea, fever, myalgia, arthralgia or rhinorrhea plus positive PCR-SARS-Cov2.

- **Asymptomatic case:** PCR-SARS-Cov2 positive in the absence of any symptoms potentially related to COVID19.

- **Case cured:** IgG serology positive with PCR-SARS-Cov2 negative and absence of symptoms.

**Background**

On December 31, 2019, the Wuhan Municipal Health and Sanitation Commission reported on a group of 27 cases of pneumonia of unknown etiology. On January 7, 2020, a new type of virus in the Coronaviridae family, SARS-CoV-2, was identified as causing this outbreak. This coronavirus has a high capacity for dissemination in hospitals, which is why health professionals have a high risk of SARS CoV2 infection as evidenced by data published in China (3,300 in early March) and estimates in Spain (about 10,000 at this time, which represents about 15% of the total registered cases, official data from the Ministry of Health). This high transmission capacity of this virus is not surprising if we consider the experience during the 2002 outbreak of severe acute respiratory syndrome (SARS), where 1,725 ​​of the health professionals (HP) were infected (Hsin DH, et al, Zou What's up.). In fact, there are several reasons that explain this high transmissibility: 1) people with a COVID19, are contagious from the beginning of the disease, that is, in the presymptomatic period, 2) the presence of the virus persists days or even weeks after disappearance of symptoms (Roman Woelfel et al.), 3) hyper-affinity to angiotensin-converting enzyme 2 receptors, causing high transmissibility, 4) false negatives, relatively common with standard techniques, 5) difficulty in establishing adequate screening circuits and in-hospital traffic (Clin Infect Dis (2020 March 12), 10.1093 / cid / ciaa255, 6) the high probability that the number of asymptomatic patients is much higher than currently admitted (R. Li et al ), 7) the difficulty in accessing adequate personal protective equipment (PPE) at times of extremely high incidence peaks, such as the current one, despite the priority given to teachers Most exposed professionals, 8) work in areas where aerosols are formed (Li Ran et al), poor hand hygiene (Lu W, et al. Sharma A, et al) and long working hours (Li D, Wu et al, Weaver MD, et al) are associated with an increase in infection in HP; and, 9) Finally, the saturation of health systems, with specific increases that may exceed 200% of normal activity, may influence this high in-hospital transmission of SARS CoV2.

**Reasons to protect healthcare professionals.** It is evident that in a scenario of sustained and widespread community transmission, maintaining the maximum operating capacity of the health system is essential. And, without a doubt, the HP are the most valuable resource of any health system (COVID-19: protecting health-care workers.). But, in addition to keeping the HP active, it is evident that there are many more reasons to protect them: 1) Firstly, for moral reasons, since the professionals we entrust our care with are exposed to potentially serious infection and As it cannot be otherwise, we have an obligation to protect. It is a legal and ethical obligation of the health authorities, 2) the infection of a HP exponentially increases the risk of transmitting the infection to the relatives with whom he lives and to the patients he treats, especially vulnerable people who have a high probability to present a severe COVID19; and, 3) very high rates of depression, anxiety and insomnia have been demonstrated in the HP exposed to this infection, which could potentially decrease with the establishment of effective chemoprophylaxis (Lai J, et al, Wang W et al).

**Predictive models**. Estimating the prevalence and spread of new undocumented coronavirus infections (SARS-CoV2) is critical to understanding the overall prevalence and pandemic potential of this disease. Li R et al suggest that 86% of all infections are undiagnosed, with the contribution of these unknown diffusers of infection being 55% of all documented cases. A very interesting epidemiological study, calculates that in our country, the diagnosis rate of this infection is probably around 5% (Timothy W et al), which explains the enormous differences in the fatality rate. The best estimates of adjusted case fatality are in the range of 1% - 1.5% (Verity R et al); Taking these estimates into account, the expected lethality can be estimated (Kucharski AJ, et al, Russell TW, et al). Long-term prediction is more complex, although a study by the Department of Multidisciplinary Mathematics at the Universitat Politècnica de València expects, in the best of scenarios, up to 800,000 infected in the coming months. Be that as it may, any of these predictive models indicate that we are underestimating the diagnoses, that this infection will accompany us until the development of a vaccine and, therefore, that the infection rate of the HP will continue to be a very important problem.

**Hydroxychloroquine. Reasons for choosing this drug.**

The reasons for the choice of HDQ over chloroquine is that it has shown increased activity against SARS CoV2 in vitro. The mechanism of action of HDQ with respect to SARS CoV2 infection is twofold, immunomodulatory, and antiviral. Its immunomodulatory capacity is largely due to the fact that it can increase intracellular pH and inhibit lysosomal activity in antigen-presenting cells, including plasmacytoid dendritic cells and B cells, thus preventing antigen processing and autoantigen presentation. class II mediated major histocompatibility complex to T cells (Lotteau V et al). This process reduces T cell activation, differentiation, and expression of costimulatory proteins and cytokines produced by T cells and B cells (Wu SF, et al / van den Borne BE, et al). Furthermore, due to altered endosome pH and disrupted binding between Toll-like receptors and their RNA / DNA ligands, TLR signaling is suppressed (Kuznik A et al / Ewald SE, et al), and thus interferes with the interaction between cytosolic DNA and the GMP-AMP synthase cyclic nucleic acid sensor (An J, Woodward JJ, et al). In this way, signaling activation decreases and cytokine production is attenuated, which justifies that HDQ could decrease the “cytokine storm”, a key phenomenon in the transition from mild to severe forms in COVID19. On the other hand, HDQ inhibits receptor binding and membrane fusion, two key steps required for cellular entry by coronavirus. It has been shown to exert an antiviral effect by interfering with the glycosylation of angiotensin-converting enzyme 2 (the cellular receptor for SARS-CoV2) and blocking the fusion of the virus with the host cell. Thus, virus binding to receptors in cells is prevented, and therefore infection is prevented. Following cell entry, HDQ concentrates on endosomes, Golgi vesicles, and lysosomes. The increase of the pH in the lysosome prevents the activity of the protease thus achieving that this fusion process is interrupted. Without the necessary pH for the endosome and lysosome to perform the excision function, coronavirus infection and replication are blocked

**Dosage and safety of HDQ:** HDQ is a safe drug, in which one of the study researchers has extensive experience. Although it is common to perform a baseline eye exam to rule out maculopathy, the truth is that doses below 5 mg / kg are safe in almost all patients. In this sense, the risk of maculopathy is close to 1% after 5-7 years of treatment, which suggests that the risk in treatments of less than 6 months duration such as the one we are proposing is minimal or negligible. Factors that increase the risk of maculopathy include high doses (> 6mg / kg / day), prolonged exposure, the presence of kidney failure or previous maculopathy and the concomitant use of tamoxifen. Another relevant and relatively frequent side effect is skin rash, sometimes extensive. Cardiac arrhythmias have been described in patients with a prolonged QTc interval, so these subjects will be excluded from the study. Also, HDQ is safe during pregnancy. The only two chemoprophylaxis trials listed on clinicaltrails.gov use the 200 mg daily dose. There is no other evidence available. For this reason, the proposed dose is 200 mg daily in a single dose.

**Efficacy of HDQ against coronavirus.** HDQ is a powerful SARS CoV inhibitor, as demonstrated years ago (Vincent et al). Most of the results are preclinical, with direct evidence of very discreet efficacy at this time. A systematic review of the efficacy and safety of chloroquine shows that preclinical and long-term safety data support the use of this drug or perhaps better HDQ in clinical trials of prophylaxis and treatment in patients with COVID19 (Cortegiani A et al. to the.). Similarly, Liu et al, publish preliminary results showing that HDQ effectively inhibits SARS-CoV-2 infection in vitro. (Liu J et al). Preliminary reports from China, South Korea, and France suggest that the treatment is at least effective in some patients. In the only clinical trial, and even though it suffers from many objectionable points, 20 patients treated with 600 mg of HDQ daily (with or without adding azithromycin) were included in a single arm trial. The treated cases showed a significant reduction in the viral load compared to the controls and a clearly shorter average duration of the disease than the untreated subjects (Gautret et al). Chinese researchers reported that treatment in more than 100 chloroquine patients was beneficial (BioScience), but the data has not yet been published. In fact, information about HDQ's effectiveness in China is proving difficult to obtain. At this time, there are a plethora of clinical trials with no results available to date. Only one ongoing trial is evaluating the role of post-exposure chemoprophylaxis.

With the aforementioned data and in the context that, in the best of cases, a vaccine will not be had before 12-18 months, the prevention of infection in HP must be an absolute priority of our healthcare system. It is evident that an optimized screening and patient traffic in hospitals (Yen MY et al), the use of PPE whenever required and extreme precautionary measures should be the axis of prevention of transmission of infection to HP . But all these measures, with the limitations existing in our country, have not demonstrated a clear efficacy in preventing SARS CoV2 infection in our professionals. For this reason, we propose this clinical trial to evaluate the safety and efficacy of HDQ chemoprophylaxis of SARS CoV2 infection in HP in the hospital setting.

**Hypothesis and expected results.** Our hypothesis is that HDQ chemoprophylaxis is capable of preventing SARS CoV-2 infection in a group at high risk of infection due to their occupational exposure and, alternatively, if it does not decrease the incidence of infection, it could be able to reduce severity. of the disease by said virus. In addition, it could potentially avoid the loss of working hours of highly qualified professionals essential in times of saturation of our health system.

In HP, HDQ chemoprophylaxis will be able to decrease the incidence of SARS-CoV-2 infection. It is less likely (although plausible) that with the dose used, the severity of the disease will decrease in the event of infection by this virus. On the other hand, the systematic study of COVID19 infection will allow us to define the incidence, prevalence and severity of SARS CoV-2 infection in healthcare personnel in the hospital setting.

**Objectives**

**Main goal:**

1) To evaluate the efficacy of HCQ prophylaxis for 2 months compared to placebo in the prevention and reduction of symptomatic and asymptomatic SARS CoV-2 infection in healthcare personnel.

**Secondary objectives.**

2) To assess the safety of HDQ for 2 months in healthcare personnel.

3) To evaluate the number of working days lost as a result of symptomatic or asymptomatic infection with COVID19.

4) To analyze the percentage of severe respiratory disease by COVID-19 in healthcare personnel.

5) To define the incidence, prevalence and severity of SARS CoV-2 infection in healthcare personnel in the hospital setting.

**Methodology. Design, study subjects, variables, data collection and analysis, and study limitations.**

**Study design.** Prospective, randomized and placebo-controlled clinical Trial. The medication will be manufactured in the Pharmacy of the Marqués de Valdecilla University Hospital (HUMV). Two groups will be analyzed with a 1: 1 randomization. The allocation to both arms will be done through the generation of a sequence of random numbers by computer. Chemoprophylaxis group (n = 225): One 200 mg HDQ tablet once daily for two months. Control group (n = 225): One placebo tablet (identical to that of the drug) once a day for two months.

**Study population.** It will include 450 health professionals who are working in areas of high exposure and high risk of transmission of SARS CoV2 (professionals from the Hospital in COVID areas, Intensive Care Unit, Emergencies, Anesthesia and all those who carry out procedures that generate aerosols).

**Inclusion criteria:** 1) Health professional aged between 18 and 65 years (inclusive) at the time of the first screening visit. 2) They must provide signed written informed consent and agree to abide by the study protocol. 3) Active work in high exposure areas during the last two weeks and during the following weeks.

**Exclusion criteria:** 1) Previous infection with SARS CoV2 (positive coronavirus PCR or positive IgG serology with SARS Cov2 negative PCR and absence of symptoms). 2) Current treatment with HDQ or chloroquine. 3) Contraindication for taking HCQ (known epilepsy, porphyria, recent ischemic heart disease). 4) Previous or current treatment with tamoxifen or raloxifene. 5) Previous eye disease, especially maculopathy. 6) Known heart failure (Grade III to IV of the New York Heart Association classification) or prolonged QTc. 7) Any type of cancer (except basal cell) in the last 5 years. 6) Refusal to give informed consent. 8) Evidence of any other unstable or clinically significant untreated immunological, endocrine, hematological, gastrointestinal, neurological, neoplastic or psychiatric illness. 9) Antibodies positive for the human immunodeficiency virus. 10) Significant kidney or liver disease. Pregnancy or lactation; Hypersensitivity or allergy to HQ, cq contraindication in data sheet to taking HQ.

**Sample size:** Taking into account the current high prevalence of infection in healthcare personnel in Spain (up to 15%), to detect a difference equal to or greater than 8% in the percentage estimates through a two-tailed 95% CI, with a statistical power of 80% and a dropout rate of 5%, a total of 450 participants will need to be included (250 in each arm).

**Intervention and comparator**Two groups will be analyzed with a 1: 1 randomization rate.

1) Intervention: (n = 225): One 200 mg hydroxychloroquine sulfate coated tablet once daily for two months.

2) Comparator (control group) (n = 225): One hydroxychloroquine placebo tablet (identical to that of the drug) once daily for two months

**Blinding (masking)**Both participants and investigators responsible for recruiting and monitoring participants will be blind to the assigned arm.

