**Case definition:**

**1) Symptomatic case:** Symptomatic COVID-19 infection defined as cough, dyspnea, fever, myalgia, arthralgia or rhinorrhea plus SARS Cov2 positive PCR.

**2) Asymptomatic case:** SARS Cov2 PCR in the absence of any symptoms potentially related to COVID19.

**3) Case cured:** IgG serology positive with SARS Cov2 negative PCR and absence of symptoms (this HP will be excluded, but gives valuable information on the prevalence of infection in HP).

**Study duration:** Twenty-five weeks, distributed as follows: 1) Recruitment period: Eight weeks from the inclusion of the first subject to the inclusion of the last study individual. 2) Screening period: After signing the informed consent, an IgG serology and coronavirus PCR will be performed, the result of which will be obtained in a maximum period of 7 days. After obtaining a negative result and corroborating a non-prolonged QTc interval, the study subject will start taking the corresponding medication. 3) Eight weeks of chemoprophylaxis vs placebo. 4) Eight weeks for database debugging and analysis of results. Preliminary publication of the first results.

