# **Diagnosis of SARS CoV2 infection.** Determination of IgA, IgM and IgG type antibodies against SARS-CoV-2 using the Anti-SARS-CoV-2 ELISA kit (EUROIMMUN Medizinische Labordiagnostika AG, Germany) every two weeks. In cases of seroconversion, a SARS-CoV-2 PCR will be performed to rule out / confirm an active infection (RT-PCR in One Step: RT performed with mastermix (Takara) and IDT probes, following protocol published and validated by the CDC Evaluation of COVID-19 in case of SARS-CoV-2 infection.

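### Exclusion 1 drops an IgG-positive, PCR-negative worker only if symptom-free, and the screening rule does not say that both tests must be negative (minor)

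*Protocol*

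**What the plan says.** Four parts of the protocol bear on a worker with SARS-CoV-2 antibodies at screening.

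- **Exclusion criteria, item 1 (Methodology).** It excludes "Previous infection with SARS CoV2 (positive coronavirus PCR or positive IgG serology with SARS Cov2 negative PCR and absence of symptoms".
- **Case definition, item 3 (the cured case).** It uses the same three conditions and adds the exclusion: "IgG serology positive with SARS Cov2 negative PCR and absence of symptoms (this HP will be excluded". The summary's case definition has the three conditions without the remark about exclusion.
- **Study duration, screening period (Methodology).** Two tests are ordered: "After signing the informed consent, an IgG serology and coronavirus PCR will be performed". Then: "After obtaining a negative result and corroborating a non-prolonged QTc interval, the study subject will start taking the corresponding medication". The summary's section on duration has the shorter form: "After obtaining a negative result, the study subject will begin taking the corresponding medication".
- **Diagnosis of SARS CoV2 infection.** Antibodies (IgA, IgM and IgG) are measured every two weeks on study, and "In cases of seroconversion, a SARS-CoV-2 PCR will be performed to rule out / confirm an active infection".

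**The concern.** The symptom condition makes sense in a definition of a cured case. In an exclusion criterion it works backwards. PCR-positive workers are already caught by the first branch, so the second branch matters only for those who are IgG-positive and PCR-negative. Requiring them to be symptom-free can only release people from exclusion, and those released have both antibody evidence of infection and current symptoms. The Background section itself counts false negatives among the reasons for spread, so a negative PCR in such a worker is limited reassurance.

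What is at stake is the infection-free baseline that a prevention endpoint needs. A participant who is IgG-positive at entry cannot seroconvert on IgG during follow-up. Seroconversion is the only trigger for PCR that the diagnosis section names. Such a participant would add to the denominator with little chance of being counted as a case.

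**Working it through.** **Step 1. Set each screening combination against the text.**

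| PCR | IgG | Symptoms | Exclusion 1 | Case definitions | Screening rule, if both tests must be negative | Screening rule, if one negative is enough |
|---|---|---|---|---|---|---|
| + | any | yes | excluded | symptomatic case | stopped | stopped if IgG is also positive |
| + | any | no | excluded | asymptomatic case | stopped | stopped if IgG is also positive |
| − | + | no | excluded | cured case | stopped | not stopped |
| − | + | yes | **not named** | **none** | stopped | **not stopped** |
| − | − | any | eligible | none | may start | may start |

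Only the fourth row is a problem. Exclusion 1 does not reach it, and the screening rule reaches it only if both tests must be negative. The row is narrow: the PCR branch of exclusion 1 has no time limit, so a worker with a documented positive PCR in the past is already out.

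**Step 2. Look for another criterion that closes the gap.** Exclusion 8 covers other unstable or untreated illness by body system, but it lists neither respiratory nor infectious disease. Nothing else in the list deals with symptoms or antibodies to SARS-CoV-2.

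**Step 3. Bound the effect.** The protocol gives no figure for this group, so there is nothing to reproduce.

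Inputs:

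- Control rate 15% and difference 8 points, from the sample-size paragraph, which begins "Taking into account the current high prevalence of infection in healthcare personnel in Spain (up to 15%), to detect a difference equal to or greater". The intervention rate is therefore 15 − 8 = 7%.
- Share *s* of participants seropositive at entry who never become cases: assumed 1% to 5%, equal in both arms. This counts every seropositive entrant, not only those missed through the symptom condition, so it is generous.

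Formula: diluted rate = planned rate × (1 − *s*).

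| *s* | Control | Intervention | Difference | Risk ratio |
|---|---|---|---|---|
| 0 | 15.00% | 7.00% | 8.00 points | 0.467 |
| 1% | 15 × 0.99 = 14.85% | 7 × 0.99 = 6.93% | 7.92 points | 0.467 |
| 5% | 15 × 0.95 = 14.25% | 7 × 0.95 = 6.65% | 7.60 points | 0.467 |

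The factor (1 − *s*) cancels in the ratio. In people, 1% to 5% of 450 is 4.5 to 22.5.

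**Step 4. Translate into power.** Take 225 per arm less 5% dropout (225 × 0.95 = 213.75, so 213). Use the two-sided 5% normal approximation for two proportions, with pooled variance under the null. Power is 75.3% at *s* = 0, 74.8% at 1% and 72.9% at 5%. The loss is 0.5 to 2.4 percentage points. The starting value is below 80% because of a separate inconsistency ("a total of 450 participants will need to be included (250 in each arm"), which has no bearing on this point.

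**The case against.** The strongest reply is that the screening rule already does the work. It orders both tests, speaks of their outcome in the singular as one result, and lets drug start only once that result is negative, with no mention of symptoms. If a negative PCR alone were enough, the IgG test ordered in the same place would play no part in the decision. Exclusion 1 is also introduced as previous infection, which points to excluding anyone seropositive. On this view the parenthesis is loose drafting borrowed from the cured-case definition, and nobody intended to admit such workers.

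Most of that stands. A reader might infer that seropositive workers with symptoms will enter the trial already infected. The documents do not support this. The natural reading of the screening rule stops them, and a worker who is PCR-negative at screening can be called previously infected but not currently infected.

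A reader might also infer that such workers would later be counted as false symptomatic cases. That is not established either. Follow-up PCR is tied to seroconversion, which they cannot show on IgG. A newly positive IgA or IgM might still trigger a PCR, but that PCR would then have to be positive after a negative one at entry. Nor is a bias between arms shown: eligibility is settled before drug starts, in a blinded trial with 1:1 allocation.

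The reply does not remove the inconsistency. The screening rule never says that both tests must be negative, and it governs the start of medication rather than eligibility. On its natural reading it bars every IgG-positive worker, while the eligibility list bars only those without symptoms.

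**Conclusion.** The point holds as a minor inconsistency. As worded, exclusion 1 does not cover the IgG-positive, PCR-negative worker with symptoms. The screening rule probably does, but it leaves open which tests must be negative. If staff apply the exclusion list literally, a previously infected worker may be enrolled, and the route to a primary event through IgG seroconversion is closed for that worker.

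The effect is likely very small. At an assumed 1% to 5% seropositive at entry, the planned difference falls from 8.0 to 7.9 or 7.6 points with the risk ratio unchanged. That range has no source in the protocol. It also assumes that these participants are spread equally over the arms and never become cases. The reason to act is a clear and consistent entry rule more than lost power.

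**What to change.** Reconcile the passages by amendment:

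1. In exclusion 1, delete the closing condition on symptoms, so that any positive SARS-CoV-2 PCR or any positive SARS-CoV-2 IgG excludes, whatever the symptoms.
2. In both descriptions of the screening period (the summary's section on duration and Study duration in the Methodology), replace the single negative result with negative results on both PCR and IgG serology.
3. Leave the cured-case definition as it is, as a descriptive category.

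The cost is two wording changes, the second made in two places. Both tests are already done at screening, so no test is added, and few extra screen failures should follow. If participants have already been randomised, their screening IgG results will show how many were positive, and that count can replace the assumed range.

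### The sample size contradicts itself (450 in total, 250 per arm, 225 per arm), and 450 gives about 76% power rather than the stated 80%

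*Protocol*

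**What the plan says.** The sample-size paragraph appears in the Methodology (Sample size) and again under Statistic analysis (Sample size estimation), with the same figures. It starts from the "current high prevalence of infection in healthcare personnel in Spain (up to 15"%), aims "to detect a difference equal to or greater than 8% in the percentage estimates" "through a two-tailed 95% CI", assumes 80% power and 5% dropout, and concludes that "a total of 450 participants will need to be included (250 in each arm").

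The rest of the protocol describes a different per-arm number. Study design in the Methodology has "Chemoprophylaxis group (n = 225): One 200 mg HDQ tablet once daily for two months" and a control group of the same size. The synopsis and the Intervention and comparator paragraph also give 225 for each arm. Study population, in both the synopsis and the Methodology, gives 450 in total. Allocation is equal: "Two groups will be analyzed with a 1: 1 randomization rate".

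**The concern.** With two equal arms, 450 in total and 250 per arm cannot both be true. The obvious guess is that 250 is a slip for 225. That guess has to be tested against the calculation, because if the stated inputs lead to 250 per arm, correcting the 250 alone would leave an 80% power claim that the trial does not meet.

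Two things depend on the answer. Recruitment, the supply of study medication from the hospital pharmacy and the length of the randomisation list need one number. And the stated power is the yardstick for a null result: at 76% power the type II error is about 24%, not 20%.

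**Working it through.** **Inputs from the sample-size paragraph.** Infection rate 15% (the only rate given); difference 8 percentage points; two-sided 5% level (two-tailed 95% interval); power 80%; dropout 5%; allocation 1:1. The test is the chi-square test named for qualitative variables under General considerations of statistical analysis. I read the rate and difference as p1 = 0.15 on placebo and p2 = 0.07 on hydroxychloroquine.

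**Consistency.** 2 × 250 = 500 and 2 × 225 = 450. The total agrees with 225 per arm and not with 250.

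**Size needed for 80% power.**

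Pooled-variance formula, with mean rate 0.11:

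n = [1.96·√(2·0.11·0.89) + 0.8416·√(0.15·0.85 + 0.07·0.93)]² / 0.08² = [0.8673 + 0.3694]² / 0.0064 = 238.9 evaluable per arm. Dividing by 0.95 gives 251.5, so 252 per arm and 504 in total.

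Unpooled formula:

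n = (1.96 + 0.8416)² · (0.1275 + 0.0651) / 0.0064 = 7.849 · 0.1926 / 0.0064 = 236.2 evaluable per arm. Dividing by 0.95 gives 248.6; rounding up to 237 first and then dividing gives 249.5, so 250 per arm and 500 in total.

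The protocol's 250 per arm is therefore reproduced. Its 450 is not.

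**Other formulas tried for 15% against 7%, with 5% dropout.**

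| Method | Per arm | Total |
|---|---|---|
| Two-sided, arcsine | 246 | 492 |
| Two-sided, unpooled | 250 | 500 |
| Two-sided, pooled | 252 | 504 |
| Two-sided, continuity-corrected | 278 | 556 |
| One-sided, no correction | 199 | 398 |
| One-sided, continuity-corrected | 225 | 450 |

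Only the one-sided, continuity-corrected version returns 450, and it contradicts the stated two-tailed interval.

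**Power at the size described.** 225 × 0.95 = 213.75, about 214 evaluable per arm. With the pooled formula, z = (0.08·√214 − 0.8673)/0.4389 = 0.690, a power of 75.5%.

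| Evaluable per arm | Pooled | Unpooled | Exact, uncorrected chi-square |
|---|---|---|---|
| 214 (450 randomised, 5% dropout) | 75.5% | 76.0% | 76.4% |
| 225 (450 randomised, no dropout) | 77.6% | 78.1% | 78.7% |
| 238 (500 randomised, 5% dropout) | 79.8% | 80.3% | 81.1% |

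A more conservative test does worse: at 214 per arm, exact power is 71.8% with Fisher's test and 71.2% with the continuity-corrected chi-square.

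**Detectable difference.** At 214 per arm, 15% against 6.6% (8.4 points) gives 80.2% by the pooled formula.

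**Sensitivity to the control rate.** For a fixed 8-point reduction at 214 per arm, pooled power is:

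| Control rate | Power |
|---|---|
| 15% | 75.5% |
| 14% | 79.0% |
| 13.5% | 80.8% |
| 13% | 82.7% |

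**The case against.** The best defence has three parts.

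First, the intended design can be identified. The total of 450 and the 225 per arm recur across the protocol, a total of 500 appears nowhere, and only the 250 is out of line. That is fair, and it makes 450 the more likely recruitment target. It does not settle the matter, because 250 is also what the stated inputs produce, so an error in the total cannot be excluded.

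Second, 7% is not stated and 15% is given as an upper limit, without being called the placebo rate. With a control rate of about 13.5% or lower and the same 8-point difference, 450 would be enough. This stands as a caveat: any power figure must carry its assumed rates. It does not rescue the 80% claim, since the protocol names no lower planning rate. The Summary and Background also describe the figure of up to 15% as the share of registered cases that occur in health professionals. That is not an eight-week infection risk, which is a further reason to state power conditionally.

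Third, the shortfall is modest: about 4 percentage points of power, or 0.4 points of detectable difference. That is true of the power on its own. The contradiction in the numbers remains whatever rates are assumed.

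**Conclusion.** The point holds. The sample-size sentence is wrong as written in both places: 450 in total and 250 per arm are incompatible under 1:1 allocation, and the arms are described elsewhere as 225. This part needs no assumption.

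For 15% against 7%, 80% power after 5% dropout needs about 500 randomised, so 450 is about 10% below that. The trial as described has about 76% power, and none of the standard two-sided calculations above reaches 80% at 450, even with no dropout. The power result rests on reading 15% as the placebo rate and 8 points as a reduction to 7%. Replacing 250 by 225 and leaving the 80% in place would not correct the statement.

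**What to change.** Make the synopsis, Study design, Sample size, Intervention and comparator, and Sample size estimation agree on one total and one per-arm number, and write out the two assumed infection rates. There are two ways to do it:

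- **Keep 450.** Write 225 in each arm and replace the power statement with: about 76% power to detect 15% against 7% (two-sided 5%) after 5% dropout, or equivalently 80% power for a difference of about 8.4 points (15% against 6.6%). This costs wording only and a slightly less favourable power figure; no participants are added.
- **Use 250 per arm.** Write 500 in total and change 225 to 250 throughout. The 80% claim then holds to within rounding (79.8% to 81.1% after dropout), at the cost of 50 more participants and the matching medication and randomisation list.

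If the sponsor planned on a control rate below 15%, the protocol should state that rate and show the calculation that leads to 450.
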